### Statistical Analysis

All analyses will be performed using intention-to-treat. For the main analysis, we will use multiple imputation for missing data. Similar to prior work [16,19], for missing step data, including values less than 1000 steps per day, we will perform 5 sets of imputations, and results will be combined using Rubin’s standard rules [38]. We will perform sensitivity analyses using available data without imputation. The primary analysis will fit a mixed effect regression model to evaluate changes in outcome measures adjusted for each participant baseline measure, time at the observation level using calendar month fixed effects, and participant random effects. Secondary analyses will fit mixed effects regression models adjusted for other variables of interest such as participant characteristics.

To understand predictors of response to the interventions, exploratory analyses will fit mixed effects regression models to evaluate associations of participant characteristics or behaviors with strong or poor performance in the outcome measures. In addition, we will use latent class analysis of the baseline variables to identify classes of participants and compare differences in their performance across the arms. We will also conduct an exploratory qualitative evaluation of the survey’s free text responses by using grounded theory to identify themes reported by the participants.

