### Baseline Step Count

Once the participants’ wearable device was setup and connected to the study, they were asked to get used to wearing the device for several weeks. During this period, a baseline step count was estimated using the second week of data—a method used in previous work [16,19]. The first week of data was ignored to diminish the potential upward bias of the estimate from higher activity during initial device use. To prevent potential mismeasurement, we ignored any daily values less than 1000 steps because evidence indicates that these values are unlikely to represent capture of the actual activity [30,31]. If less than 4 days of data were available during the second week, the patient was contacted to inquire about any device issues, and the run-in period was expanded until at least four days of data were captured.

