### Interventions

Participants in the control arm used the devices but received no other interventions and were not asked to conduct goal setting. Participants randomized to 1 of the 3 gamification arms conducted goal setting during the in-person visit. This included selecting a HbA_1c_ reduction goal (1.5%, 2%, or 2.5%), a weight loss goal (6%, 7%, or 8% of their baseline weight), or an increase in daily step counts (33%, 40%, or 50% greater than baseline, or any step goal that is at least 1500 steps above their baseline). A number of design considerations were incorporated to help participants achieve their goals while minimizing risks. First, the weight loss goal was set for a gradual decline over the first 26 weeks and then to maintain that level during the next 26 weeks. Participants were given a weight target each week, and if not achieved, the target remained the same for the following week. Second, participants had a 4-week ramp up toward their daily step goal. For example, a participant with a baseline of 6000 steps per day and goal of 8000 steps per day was asked to achieve goals of 6500, 7000, 7500, and 8000 for each of the first 4 weeks of the study. Then, they were asked to maintain the 8000 steps per day goal for the remainder of the study. Finally, the HbA_1c_ goal was set for the 6-month time point and was expected to be maintained through 1 year.

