Participants in the gamification arms were entered into an intervention approach based on prior work that used points and levels designed to incorporate insights from behavioral economics [19,20]. First, participants were asked to sign a precommitment pledge to strive to achieve their goals during the study. Precommitment has been demonstrated to motivate behavior change [32,33]. Second, at the beginning of each week, the participant received 70 points (10 for each day that week). If the participant did not weigh-in, they lost 10 points from their balance. This leverages loss aversion, which has demonstrated that loss framing is more effective at motivating behavior change than gain framing [14-16]. Third, at the end of each week, if participants had at least 40 points, achieved their weekly weight target, and averaged at or above their daily step goal, they were moved up a level (levels from lowest to highest: blue, bronze, silver, gold, and platinum). If not, participants were dropped a level. This design creates achievable goal gradients—the notion that the next highest level was attainable—and a sense of social status and progression through the game. All participants begin at the silver level, so that they will feel the loss of dropping to bronze if they do not achieve enough points in the first week. Participants who finished in the platinum level received a trophy, and participants who finished in the gold level received a medal. Fourth, participants got a new set of 70 points every Monday. This design leverages the *fresh start effect* that is the tendency for aspirational behavior around temporal landmarks such as the beginning of the year, month, or week [34]. Fifth, to help re-engage participants who are struggling to meet their goals at months 3, 6, and 9 (defined as being in the blue or bronze levels of the game), the study coordinators called them to inquire about their progress in the study, reset them to the silver level, and offered them the opportunity to readjust their goals based on their initial options. Sixth, the participants’ primary care physician was mailed a monthly report with data on their change in weight, step goals, HbA_1c_, and LDL-C (Figure 2). A copy of this letter was also mailed to the participant. Finally, the game varied based on the social incentive arm described as follows:

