### Outcome Measures

The primary outcomes were change in HbA_1c_, change in weight in pounds, and change in mean daily steps from baseline to the end of the 1-year study. Secondary outcomes include the change in LDL-C levels from baseline to end of the 1-year study, and change in mean daily steps, weight in pounds, and HbA_1c_ from baseline to the 6-month time point of the study.

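### Steps outcome: five imputations leave a near-threshold result dependent on the random seed, and the one sensitivity analysis named does not test informative non-wear

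*Protocol article*

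**What the plan says.** All of the following is in the protocol article.

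- **Outcome Measures** lists "change in mean daily steps from baseline to the end of the 1-year study" among the three primary outcomes. **Power** sets a two-sided level of 0.017.
- **Statistical Analysis**: "For the main analysis, we will use multiple imputation for missing data". For steps, "for missing step data, including values less than 1000 steps per day, we will perform 5 sets of imputations", pooled by Rubin's rules. The model is fixed too: "The primary analysis will fit a mixed effect regression model to evaluate changes in outcome measures adjusted for each participant baseline measure", with calendar-month fixed effects and participant random effects.
- The robustness check in the same section is "We will perform sensitivity analyses using available data without imputation". No other is named, and no missing-data mechanism or imputation model is given.
- **Baseline Step Count** gives the reason for the cut-off: "we ignored any daily values less than 1000 steps because evidence indicates that these values are unlikely to represent capture of the actual activity".
- **Interventions** separates the arms: "Participants in the control arm used the devices but received no other interventions". In the gamification arms, participants who had enough points, met the weight target and "averaged at or above their daily step goal, they were moved up a level".

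**The concern.** There are three linked issues, all about choices that the article does make.

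1. **Absent days.** Standard multiple imputation and a likelihood-based mixed model on available data both need missing at random. If people leave the device off on inactive days, or after falling behind in the game, both methods can be wrong in the same direction, and their agreement would not reveal it. Arm-dependent wear is plausible because recorded steps affect game level in three arms and nothing in control.
2. **Recorded values below 1000.** The main analysis replaces them by imputation. The article does not say whether the available-data analysis keeps them, so no analysis is clearly stated to vary the cut-off.
3. **Number of imputations.** With five, the pooled estimate and its standard error carry simulation noise. Near 0.017 that noise can decide significance. Under the two-phase procedure in Power it can also decide which arms go on to be compared with each other.

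**Working it through.** **Step 1. The plan's own figure.** Inputs from Power: 90 per arm, 10% dropout, so 90 × 0.9 = 81; target 1100 steps; SD 2000; two-sided 0.017 (critical value 2.387).

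- Expected z = 1100 / (2000 × √(2/81)) = 1100 / 314.3 = 3.50.
- Power = Φ(3.50 − 2.387) = 86.7%.

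The stated minimum of 80% for steps reproduces and is not in dispute. The value 3.50 is used again in Step 3.

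**Step 2. Informative non-wear.** Let f be the share of days without data in an arm, and D the amount by which true steps on those days fall below the imputed mean. Then

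bias in the arm contrast = f(int) × D(int) − f(ctrl) × D(ctrl), which with a common D is D × (f(int) − f(ctrl)).

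The article gives neither f nor D, so both are assumed:

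| Difference in missing share | D (steps) | Shift (steps) | Share of 1100 |
|---|---|---|---|
| 0 | any common value | 0 | 0% |
| 10 points | 1000 | 100 | 9% |
| 20 points | 1500 | 300 | 27% |

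With D positive, more missing days in the intervention arm inflate the contrast, and more in control shrink it. A wider assumption of 20 points and D = 4000 gives 800 steps. A mixed model on available data in effect fills absent days from observed ones, so it carries much the same bias.

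**Step 3. Five imputations.** Let γ be the fraction of missing information. The article does not give it; 10% to 30% is assumed. Scale the total variance with unlimited imputations to 1, so that the between-imputation part is γ and the within part is 1 − γ. With m imputations:

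- the pooled estimate varies across seeds around its limit z with variance γ/m;
- the estimated between-part is B = γ × χ²(m−1)/(m−1);
- T = (1 − γ) + (1 + 1/m)B and λ = (1 + 1/m)B/T;
- the Barnard-Rubin degrees of freedom ν satisfy 1/ν = λ²/(m − 1) + 1/[(161/163) × 160 × (1 − λ)], with 2 × 81 − 2 = 160 complete-data degrees of freedom.

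Worked interval width at γ = 0.2, with B at its expected value:

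- m = 5: T = 0.8 + 1.2 × 0.2 = 1.04; λ = 0.231; ν = 46.4; t = 2.476; half-width √1.04 × 2.476 = 2.525.
- m = 50: T = 0.8 + 1.02 × 0.2 = 1.004; λ = 0.203; ν = 113.8; t = 2.422; half-width 2.427.
- Ratio 2.525 / 2.427 = 1.040.

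The last four columns show the simulated share of seeds with p < 0.017. The limit z = 2.6 corresponds to p of about 0.010:

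| γ | Width, m = 5 to m = 50 | z = 2.6, m = 5 | z = 2.6, m = 20 | z = 2.6, m = 50 | z = 3.5, m = 5 |
|---|---|---|---|---|---|
| 10% | 1.015 | 79% | 98% | about 100% | about 100% |
| 20% | 1.040 | 63% | 88% | 98% | 99% |
| 30% | 1.077 | 54% | 78% | 93% | 94% |

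**Step 4. Effect on power.** Multiply the standard error by √(1 + γ/m) and use a t reference with (m − 1)/γ² degrees of freedom, holding the SD at 2000. Steps power at m = 5 is 85.7% at γ = 10% and 81.7% at 30%, against 86.6% and 86.3% at m = 50. It falls below 80% only at a γ of about 40% (78.4%).

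**The case against.** **The article is a condensed document.** A full SAP may contain tipping-point analyses, more imputations or a rich imputation model. This stands: a reader might infer that no other sensitivity analysis exists, but the article shows only that none is named in it.

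**Missing at random is not stated.** Correct. It is inferred from the standard use of multiple imputation with Rubin's rules and of mixed models.

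**The check is not empty.** A reader might infer that the available-data analysis is bound to agree with the main one. It is not: the two can condition on different variables, and if recorded values below 1000 are kept, it already varies that rule. A reader might equally infer that those values are dropped, since the article classes them as missing, but it does not say so. What stands is narrower: for absent days, agreement would not test informative non-wear.

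**The cut-off is not arbitrary.** Baseline Step Count gives a measurement reason, and the same threshold applies at baseline and follow-up. This stands. It supports treating such values as suspect, but does not show that those days resemble observed ones.

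**Differential wear is not documented.** All arms use the device, daily points depend on weigh-ins, and steps enter only the weekly level decision. The link is plausible and no more.

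**The seed example sits close to the threshold.** True. At the design effect the call is nearly always stable, and at 5% missing information 93% of seeds agree even at z = 2.6 with m = 5. Moreover, 20 imputations would remove much of the problem, so 50 is a convenient choice and not a necessary minimum.

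**Conclusion.** The concern holds in limited form and is worth acting on.

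- The one check named in the article does not address informative non-wear in a primary outcome. The possible shift is 100 to 300 steps in either direction under the assumed inputs, and zero if shares and shortfalls are equal. The documents do not support saying that such a bias exists or which way it runs.
- The handling of recorded values below 1000 in the available-data analysis is unclear and needs one sentence.
- Five imputations is a weakness of precision and reproducibility. It is neither a bias nor an error. At 10% to 30% missing information, intervals are 1.5% to 8% wider than with 50, and a result at z = 2.6 is significant in 79% to 54% of seeds, against about 100% to 93%. At z of about 3.5 the call holds in 94% or more.

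The stated power for steps is unaffected as a claim: it still exceeds 80% with five imputations up to 30% missing information.

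**What to change.** Keep the main analysis and model. Unless the full SAP already provides for them, make these changes before unblinding:

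1. Raise the number of imputations for steps from 5 to about 50, and record the seed.
2. State whether recorded values below 1000 are kept in the available-data analysis, and specify one sensitivity analysis that keeps them as observed.
3. Add a delta-adjusted imputation for steps on days without data, lowering imputed values by, for example, 500 to 2000 steps, in one arm at a time and in all arms. Report the shift at which the conclusion changes, alongside the share of days without data by arm.

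The cost is computing time and two extra tables. No new data are needed.

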### In-Person Visit and Randomization

After a baseline step count had been established, the participant was scheduled for an in-person visit with the study team to complete the enrollment process. During this visit, all participants received education on the importance of diet and physical activity for weight loss and glycemic control. The participants were provided with a wireless weight scale and had a baseline weight measured (Figure 1). As weight can fluctuate based on time of day and clothing, we monitored for weights taken at home that were >5 lbs different. In those cases, the study team reached out to participants to clarify the most accurate weight to use as his or her baseline. At the in-person visit, participants were then randomized to one of the study arms. A participant was considered ready to be randomized once he or she had completed all surveys, established a baseline step count, completed baseline laboratory work for HbA_1c_ and LDL-C, and had come in for an in-person study visit to establish a baseline weight measurement. Randomization was conducted electronically using block sizes of 4 groups with 3 participants per group. The first participant in the group was randomly assigned to an arm, and the next 2 participants were assigned to fill that group. In most cases, the participants in a group did not previously know each other. However, if 2 participants did know each other and wanted to join together, then they were randomized together as either groups of 2 or 3 persons. Participants were informed of their arm assignment during the in-person visit with the opportunity to ask any questions related to the intervention design.

All investigators, statisticians, and data analysts were blinded to arm assignments until the study and analysis were completed.

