In the supportive social incentive arm, participants were asked to identify a family member or friend to be their support sponsor. This sponsor is encouraged to support the participant in their progress during the study. A weekly report is sent by email to the sponsors with the participants’ performance including their points and level (Figure 3).In the competitive social incentive arm, participants are placed into a group of 3 participants. These participants typically did not know each other before the study but were introduced to each other by email at the beginning of the intervention. At the end of each week, the participants receive an email with a leaderboard that ranks them on their cumulative points in the study thus far and also displays their level. In the event of a tie in total cumulative points, the participants will be secondarily ranked on level. This feedback may help to induce participants to compete for the top spot among the group.In the collaborative social incentive arm, participants are placed into a group of 3 participants as a team. These participants typically did not know each other before the study but were introduced to each other by email at the beginning of the intervention. Each day, one of the members of the group is randomly selected to represent his or her team for that day, and that information is shared with the entire group. If the participant selected weighed in on the previous day, the team keeps their points. If he or she did not, then the team is told that they lost 10 points. In this design, each person is accountable to the others in the team, and this may induce a collaborative effort to meet their daily goals. The entire team moves up a level only if the team has at least 40 points by the end of the week.

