### Power

We estimated that a sample size of 360 participants (90 per arm) will provide at least 80% power using a conservative Bonferroni adjustment of the type I error rate with a 2-sided alpha of .017 and accounting for a dropout rate of 10% to detect (1) an 1100-step change in physical activity with a standard deviation of 2000 steps; (2) a 6-lb change in weight with a standard deviation of 10 lbs; and (3) a 0.8% change in HbA_1c_ with a standard deviation of 1.5%. These values are based on prior work [19,20,35,36]. This trial has been powered for 2 phases of hypothesis testing. In the first phase, we will compare each of the 3 intervention arms with control. In the second phase, we will compare successful intervention arms with each other. We expect that the magnitude of difference between intervention arms will be less than that of successful intervention arms compared with control. For this second phase of analyses, we will use a conservative Bonferroni adjustment of the type I error rate with a 2-sided alpha of .017 to adjust for up to 3 comparisons. As only intervention arms that demonstrated a significant difference with the control are compared with each other in the second phase, the overall family-wise error rate of this 2-phase procedure is controlled at 0.05 [37].

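### Participants are allocated in groups of 3, and treated as groups in two arms, but the stated primary model and power inputs ignore correlation within groups

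*Protocol article*

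**What the plan says.** **Allocation (In-Person Visit and Randomization).** Blocks contain 4 groups of 3 participants. "The first participant in the group was randomly assigned to an arm, and the next 2 participants were assigned to fill that group". People who know each other and wish to join together are randomized jointly in twos or threes. No arm is exempted.

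**Treatment (Interventions).** In the competitive arm, three participants share a weekly leaderboard that ranks them individually. In the collaborative arm, three participants share points and level: "The entire team moves up a level only if the team has at least 40 points by the end of the week". The supportive arm uses a sponsor chosen by each participant. Control participants only use the devices.

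**Model (Statistical Analysis).** The primary mixed model is "adjusted for each participant baseline measure, time at the observation level using calendar month fixed effects, and participant random effects". Neither the secondary nor the sensitivity analyses described there add a group term or a cluster-robust variance.

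**Power.** The article states that "a sample size of 360 participants (90 per arm) will provide at least 80% power". The inputs are a difference and a standard deviation for each outcome, a two-sided alpha of 0.017 and 10% dropout. No ICC or design effect is among them. The same section says that the two-phase procedure holds the family-wise error rate at 0.05.

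**The concern.** The group is the unit of allocation in every arm and the unit of treatment in two. In the collaborative arm members are meant to feel accountable to one another, so influence between members is part of the intended mechanism. Outcomes within a group may therefore be correlated.

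The random effects named in the model sit at the participant level. They handle several observations on one person and leave members of the same group independent of each other. If the within-group correlation is positive, the model overstates the information in the data: intervals are too narrow and tests reject too often. The effect is largest for competitive versus collaborative, where both sides are made of groups that interact.

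The family-wise claim takes each test to have its nominal size of 0.017. The power statement likewise takes 81 evaluable participants per arm as 81 independent units.

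**Working it through.** **Inputs from the Power section.** 90 per arm, and 90 × 0.9 = 81 evaluable; two-sided alpha 0.017. Standardized effects: HbA1c 0.8/1.5 = 0.533; steps 1100/2000 = 0.55; weight 6/10 = 0.60.

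**Assumptions.** Group size is m = 3, from the randomization section. The ICC is not given, so a range of 0.01 to 0.20 is assumed. It is taken as positive and equal in the clustered arms.

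**Step 1: the plan's own figure.** Two-sample t-test with 81 per arm, 160 degrees of freedom and noncentrality d × √(81/2):

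| Outcome | Noncentrality | Power |
|---|---|---|
| HbA1c | 3.39 | 83.6% |
| Steps | 3.50 | 86.0% |
| Weight | 3.82 | 91.9% |

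The normal approximation gives 84.3%, 86.7% and 92.4%. The claim of at least 80% reproduces for independent participants.

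**Step 2: variance inflation.** The design effect within a clustered arm is 1 + (m − 1) × ICC = 1 + 2 × ICC. The variance of a difference between arms is then multiplied by:
- one arm clustered (competitive or collaborative versus control, with control participants independent): (1 + 1 + 2 × ICC)/2 = 1 + ICC;
- both arms clustered (competitive versus collaborative): 1 + 2 × ICC.

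**Step 3: true size of a nominal 0.017 test that ignores the group.** Size = 2 × [1 − Φ(2.387/√factor)], where 2.387 is the two-sided normal critical value for 0.017.

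| ICC | One arm clustered | Both arms clustered |
|---|---|---|
| 0.01 | 0.0176 | 0.0181 |
| 0.02 | 0.0181 | 0.0193 |
| 0.05 | 0.020 | 0.023 |
| 0.10 | 0.023 | 0.029 |
| 0.20 | 0.029 | 0.044 |

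Worked case, ICC 0.20 with both arms clustered: factor 1.40, √1.40 = 1.183, 2.387/1.183 = 2.017, size 0.044. The true standard error is then 1.183 times the one the model reports. With one arm clustered the ratio is √1.20 = 1.095.

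**Step 4: power under an analysis that respects the groups.** Divide the standardized effect by √factor and repeat Step 1. The ICC above which power drops below 80% is:

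| Outcome | One arm clustered | Both arms clustered |
|---|---|---|
| HbA1c | 0.086 | 0.043 |
| Steps | 0.155 | 0.077 |
| Weight | 0.374 | 0.187 |

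The normal approximation gives slightly higher thresholds (HbA1c 0.105 and 0.053; steps 0.176 and 0.088; weight 0.399 and 0.199). At ICC 0.02, HbA1c power is still 82.7% (one arm) or 81.9% (both). At ICC 0.20 it is 75.3% or 67.6%.

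**The case against.** **The correlation may be small.** The article says that most group members had not met before the study, and in the two group arms they were introduced by email. Supportive and control participants share only their allocation. At an ICC of 0.01 to 0.02 the test size moves from 0.017 to at most 0.0193. Competition need not make members alike, so a positive ICC is itself an assumption. This stands, and it limits the likely size of the problem. It does not justify leaving the term out, because the model would then give no sign if the correlation were larger.

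**A reader might infer that the stated 80% power is wrong.** The document does not support that. It claims at least 80%, its own inputs give 83.6% to 91.9%, and that margin absorbs a modest ICC. Without an ICC, no shortfall can be shown.

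**The lowest power figures need care.** The case with both arms clustered is competitive versus collaborative, which is tested only if both arms first beat control. The Power section expects smaller differences there, so 67.6% at the full 0.8-point effect is not a planning scenario for that phase.

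**A reader might also treat the two group arms alike, or blame the missing term for unequal precision between arms.** Shared points and level belong to the collaborative arm only. Any difference in precision would come from the design, not from the model.

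**The article is condensed.** A full analysis plan may contain a group term. But the article lists the fixed and random effects of its primary model, and the group is not among them.

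**Conclusion.** The point holds for the model. Groups are allocated whole in every arm and treated as groups in two, and the primary model as written has no means of capturing correlation between members. For any positive ICC, tests involving the competitive or collaborative arm exceed their nominal 0.017: about 0.018 to 0.029 against control and 0.018 to 0.044 against each other, over an assumed ICC of 0.01 to 0.20. The family-wise claim is therefore not assured.

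For power the point is narrower. The statement is correct under independence and needs that qualification. HbA1c has the least room, steps have more, and weight is robust to a considerable ICC.

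These figures rest on groups of 3 and on independence among control participants. If shared allocation alone induced similar correlation in the control triplets, comparisons with control would move to the columns for both arms clustered. With dropout, an average of 2.7 evaluable members (3 × 0.9) would soften the effect: at ICC 0.20 the sizes become 0.027 and 0.039.

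**What to change.** 1. Add a random intercept for the randomized group to the primary model, with participants nested in groups in all arms and the group variance allowed to differ by arm. Cluster-robust standard errors on the group identifier are an acceptable alternative. Either one is enough.
2. Treat acquaintance groups of 2 or 3 as groups under the same identifier.
3. Report the estimated ICC for each primary outcome.
4. Qualify the power statement as assuming no clustering, and give the ICC at which each outcome falls below 80%. Recruitment has closed, so this changes the description and not the sample size.

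The cost is one extra model term, slightly wider intervals and a slightly lower stated power. If the ICC is near zero, little is lost. The article says that analyses are still to be reported and that analysts stay blinded until the analysis is complete, so the change can be made without knowledge of results by arm. If a full analysis plan already contains a group term, the article's description of the model should be brought into line with it.
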